### ECT procedures

ECT will be administered three times per week (Mondays, Wednesdays, and Fridays), according to the standard protocol of the Mental Health Services in the Capital Region of Denmark. Patients are anesthetized with thiopental, and succinylcholine is administered for muscle relaxation. Bitemporal (BT) electrode placement with an energy dosage 1.5 times above the seizure threshold can be changed to right unilateral (RUL) treatment in the case of severe cognitive side effects; this is decided by the treating psychiatrist. The dosing strategy with the initial dose is based on patient age (charge [percentage of 500 millicoulombs] = 50% of the age). Subsequent treatments are dose-titrated based on seizure quality. The end of treatment is determined by the treating psychiatrist.

### Randomization and blinding

Power calculation and block randomization have been conducted by the independent *Pharma Consulting Group AB* (www.pharmaconsultinggroup.com) using PROC POWER and the SAS code in the Statistical Analysis Software (SAS) version 3. Treatment groups are stratified for age (≥ 40 or < 40) and gender. At the time of inclusion, gender and date of birth are registered to determine the appropriate stratum for each included patient. Study identification numbers are provided consecutively within each stratum. Patients and outcome assessors are blinded to treatment assignment, and blinding is maintained throughout the study period and the data analysis. The randomization list is kept in a locked filing cabinet for which only the person preparing the study medication and the principal investigator have a key. Preparation of study medication is performed to ensure double-blinding at the time of infusion: 1 ml recombinant human EPO (Eprex; 40,000 IU; Janssen-Cilag) or saline (NaCl 0.9%) kept at a temperature of 5–8 °C is injected into a standard 100 ml saline (NaCl 0.9%) infusion bag, which is then given to the study nurse or physician administering the medication. Double-blinding is further ensured by EPO being a colorless liquid undistinguishable from saline. Weekly monitoring of blood tests and any side effects of EPO treatment are performed by a physician not involved in outcome measure assessments. Participants are instructed to not reveal any symptoms or potential physical side effects associated with EPO treatment to study personnel involved in outcome assessments. The Good Clinical Practice (GCP) Unit at Copenhagen University Hospital (www.gcp-enhed.dk/kbh) will monitor that blinding is maintained. Unblinding for individual participants is permitted for safety reasons in cases of side effects or serious adverse events likely or directly related to the study medication. Revealing a patient’s allocated intervention during the trial involves opening his or her sealed randomization envelope. In these cases, it is the sovereign decision of [name], [name], MV, or [name] as to whether the randomization code should be broken.

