## Methods/design

### Participants and screening

A total of 52 patients with major depression (MDD) or BD scheduled for ECT treatment will be recruited from Psychiatric Centers in The Mental Health Services in the Capital Region of Denmark. Half of the participants will be randomized to receive active EPO treatment (*n* = 26), while the other half will receive a placebo (saline) (*n* = 26).

Prior to enrollment, patients will be screened with the *Mini International Neuropsychiatric Interview* (MINI) [26] to confirm their International Statistical Classification of Diseases and Related Health Problems (ICD-10) diagnosis. Eligible patients have a diagnosis of MDD, unipolar disorder (UD), or BD with current moderate to severe depressive episode symptoms, a Hamilton Depression Rating Scale, 17 items (HDRS-17) score ≥ 17 [27], are 18–70 years of age, have fluent Danish skills, and are able to provide informed consent. Exclusion criteria are treatment under involuntary measures, previous ECT within the last 3 months, other neuropsychiatric conditions, alcohol or substance misuse disorder, or recent suicide attempts. To ensure the safety of the EPO treatment, patients are also excluded if they have a significant medical condition (including diabetes, renal failure, heart disease, epilepsy, untreated/insufficiently treated hypertension, malignancies, or thromboses), are pregnant, use contraceptive medication, or have a family history of thromboses or epilepsy, similar to our previous studies [28]. Pregnancy tests are mandatory for and will be performed on female patients in their fertile age before their inclusion in the trial. Patients will also be excluded if they are overweight (body mass index (BMI) > 30) or have a body weight < 45/> 95 kg. Blood screening and physical examinations are undertaken at baseline and weekly during the 3-week EPO treatment period to ensure patient safety. These exclusion criteria and weekly safety monitoring prevented serious adverse events in our previous EPO trials [8, 9, 28]. Written informed consent is obtained by one of the named authors before inclusion. The procedures are in accordance with the ethical standards of the Danish Research Ethics Committee for the Capital Region.

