**Fig. 1 Fig1:**
[figure not shown]
Schedule of enrollment, interventions, and assessments. Abbreviations: *AMI-SF* Columbia University Autobiographical Memory Interview-Short Form, *RAVLT* Rey Auditory Verbal Learning Test, *TMT-B* Trail Making Test Part B, *WAIS-III LNS* Wechsler Adult Intelligence Scale Version III Letter-Number Sequencing, *RBANS Coding* Repeatable Battery for the Assessment of Neuropsychological Status Coding, *RVP* Rapid Visual Processing (*CANTAB* Cambridge Cognition Ltd.), *HDRS-17* Hamilton Depression Rating Scale, 17-item version, *BDI-21* Beck Depression Inventory, 21 items, *COBRA* Cognitive Complaints in Bipolar Disorder Rating Assessment, *CTQ* Childhood Trauma Questionnaire

EPO is kept at 2–8 °C during transport and storage to minimize the risk of damaging the medication and potential side effects. EPO will be dissolved in 100 ml saline and administered intravenously over 15 min. Patients will stay at the clinic for observation for at least 30 min after each infusion in case of acute severe adverse events. In cases of significantly increased hematocrit (men > 50%, women > 48%) at two consecutive blood test measurements within the same week, bloodletting (450 ml) will be performed on a weekly basis with no cessation of treatment until hematocrit values are normalized. In the case of a significant increase in thrombocytes (> 400 billion/L) or a drop in reticulocytes (< 1‰), two repeated controls will be performed in the following week. If the values stay abnormal, the patient will be withdrawn from further study participation and monitored with weekly medical examinations and blood samples until he or she is stabilized. If deemed necessary by the medic responsible for patient safety, the patient might be hospitalized for observation. Procedures for breaking randomization codes are established in the case of serious adverse events potentially or directly related to the medical intervention. These procedures will be followed if knowledge of the patient’s medical treatment will have implications for treatment of the observed serious adverse events. The principal investigator or any medical doctor responsible for the patient is able to decide whether to break emergency envelopes for potentially affected patients.

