### Data management and monitoring

Personal information is obtained at enrollment or from patient records, if patients are unable to provide the necessary information. Written informed consent forms will be signed and kept in a locked filing cabinet, and a password-protected list that matches participant ID numbers with personal information will be stored isolated from pseudo-anonymized data. A list matching participants’ personal information with their ID number will be deleted, while consent forms are maculated 10 years after study completion, after which all data will be completely anonymized. All named authors will have access to the final dataset. Pseudo-anonymized data will be entered in the *Research Electronic Data Capture* (REDCap) database, which fulfills the Danish data law for keeping patients’ records and meets GCP requirements for data management. Study personnel responsible for outcome assessments and evaluation of the findings are blinded to study medication until the data analyses are completed. Consequently, blood sample results and lists of potential adverse effects are registered in REDCap slots to which only medical doctors responsible for patient safety and the person involved in blinding of the study medication have access. Data quality is heightened by verification of data entered by outcome assessors and range restrictions on values from neuropsychological test and questionnaire scores. In addition, REDCap has a logging module which enables tracking of the entered data. As an additional precaution, registration of all primary outcome data will be double-checked by [name].

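### The principal investigator can reach the full randomisation list with no stated separation from enrolment or evaluation, and two sections give different code-break rules

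*Protocol article*

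**What the plan says.** All references are to the protocol article.

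**Generation and custody of the list.** Randomization and blinding says that an outside company prepared the sequence: "Power calculation and block randomization have been conducted by the independent" firm. Strata are formed by age (below 40, or 40 and above) and gender. Numbering is sequential: "Study identification numbers are provided consecutively within each stratum". The list is locked in a cabinet "for which only the person preparing the study medication and the principal investigator have a key".

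**Blinding promises.** Randomization and blinding covers patients and outcome assessors, through the study period and the data analysis. Data management and monitoring goes further: "Study personnel responsible for outcome assessments and evaluation of the findings are blinded to study medication until the data analyses are completed".

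**Enrolment.** Participants and screening says: "Written informed consent is obtained by one of the named authors before inclusion". It does not say whether the principal investigator is one of those taking consent.

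**Code breaks.** Study design and procedures (text after Fig. 1) provides for breaking the code "in the case of serious adverse events potentially or directly related to the medical intervention", when knowing the treatment matters for managing the event. The principal investigator or any doctor responsible for the patient decides. Randomization and blinding permits unblinding for safety reasons "in cases of side effects or serious adverse events likely or directly related to the study medication", by opening that patient's sealed envelope. The decision rests with four listed individuals.

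**The concern.** Commissioning an independent company to generate the sequence protects concealment only while nobody involved in recruiting can read it. Here the person who leads the trial can open the cabinet. If that person also decides on inclusions, knowing the next assignment could affect who enters and when. If that person also weighs withdrawals, code breaks or analysis choices, those judgements would no longer be blind. Neither effect can be detected afterwards from the data alone, and reading a list leaves no trace.

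The two code-break rules raise a separate problem. If staff can point to either section, the same event may lead to unblinding in one case and not in another. The number of unblinded patients then depends partly on which text was followed.

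**Working it through.** The point turns on text, not on a calculated figure, so the sections are set side by side.

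**Step 1: what the key gives access to.**
- Strata: 2 age groups × 2 genders = 4.
- Planned patients: 52, so on average 52 / 4 = 13 per stratum.
- With a pre-generated blocked list and consecutive numbers within each stratum, the next unused line in a stratum is the next patient's arm. A reader of the list therefore need not guess at block patterns.

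**Step 2: whether the access is needed.** Both code-break texts work through envelopes opened for the individual patient. Under Study design and procedures the principal investigator may already decide on opening one. The article gives no other task for which this role needs the list. What the key adds is sight of every patient's arm, including those not yet enrolled.

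**Step 3: whether the roles are kept apart.**

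| Task | What the article states | Principal investigator excluded? |
|---|---|---|
| Taking consent | One of the named authors | Not stated |
| Outcome assessment | Assessors are blinded | Not stated |
| Evaluation of findings | Personnel blinded until the analyses are completed | Not stated |
| Blood results and adverse-effect lists | Restricted to safety doctors and the person involved in blinding the medication | Not listed by role |

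The last row shows an imbalance. Indirect clues to allocation are fenced off with care, while the list itself is open to a role for which no separation is stated. By contrast, the physician who monitors safety is expressly kept out of outcome assessment.

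**Step 4: the two code-break rules.**

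| Element | Study design and procedures | Randomization and blinding |
|---|---|---|
| Event | Serious adverse events only | Side effects as well as serious adverse events |
| Weakest qualifying link to treatment | Potential | Likely |
| Condition | Knowledge must bear on treating the event | Safety reasons, with no such condition |
| Who decides | Principal investigator or any doctor responsible for the patient | A closed list of four individuals |

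Neither rule contains the other:
- A non-serious side effect that is likely related falls under the second rule only.
- A serious event that is potentially but not likely related, where knowledge would affect its treatment, falls under the first only.
- A responsible doctor who is not one of the four may decide under the first rule but not under the second.

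**The case against.** The strongest reply is that a key is access, not use. Nothing says that the principal investigator opens the cabinet, enrols patients, assigns numbers, tests patients or evaluates results. A condensed article may also leave the delegation of duties to the full protocol. Safeguards are stated: the GCP Unit monitors blinding, a separate physician handles safety, and safety data are held in restricted database fields. All of this stands and limits what can be claimed. It does not remove the point, because the custody arrangement is itself stated and it permits the access.

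Four stronger readings are tempting but not supported.

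- **That concealment is broken, or the blinding promise contradicted.** Both would require the principal investigator to enrol, assess or evaluate. No passage says so. An unblinded principal investigator kept away from those tasks would satisfy both blinding statements.
- **That the next arm is known with certainty for all 52 patients.** That assumes that the list is consulted and that one person controls every inclusion, although treatment and assessment take place at three centres.
- **That the earlier trials' rates, 5 / 35 = 14% for bloodletting and 6 / 35 = 17% for stopping because of thrombocytes, measure how often EPO patients would be unblinded.** Those trials gave eight weekly infusions. Safety procedures and monitoring reports one bloodletting in week 3 (1 / 35 = 3%), treatment stops for thrombocytes only after 5–7 weeks, and no expectation of such effects in this trial. The article handles these laboratory findings without mentioning a code break.
- **That the second code-break rule is simply looser.** It is wider on event type and condition but narrower on causality and on who decides.

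Three of the four decision-makers' names were removed and the fourth appears as initials. How far the two groups differ in practice therefore cannot be checked, although any responsible doctor and a closed list are different rules as written.

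**Conclusion.** The point holds as a risk in a stated arrangement. The principal investigator can reach the full list, the article gives no need for this, and it states no separation from enrolment, assessment or evaluation. Concealment and the promise of blinding until the analyses are completed therefore depend on the key not being used, or on a division of roles that the article does not state. The exposure is the whole list: 52 planned patients, on average 13 per stratum. No size of bias can be derived from the documents, and none is claimed. If the full protocol excludes the principal investigator from those tasks, the risk shrinks to a matter of wording.

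The code-break discrepancy rests on no assumption about anyone's role. The two texts differ in four elements and must be reconciled; this review takes no position on which rule is right. The change is worth making because it costs almost nothing, but the documents show no breach.

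**What to change.** 1. In Randomization and blinding, change the custody sentence so that only the unblinded person preparing the study medication, or the external randomisation provider, can reach the list. The principal investigator relies on the individual sealed envelopes.
2. Log every envelope opening (date, role, reason) and report the number opened by arm.
3. Bring the code-break texts in Study design and procedures and in Randomization and blinding to one statement of event, causality, condition and deciding roles. The choice among these belongs to the sponsor and the investigators.

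If the key cannot be withdrawn, a weaker alternative is to state that the principal investigator takes no part in enrolment, outcome assessment or analysis.

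The cost is one key handed over, a log sheet and a wording change. Sample size, schedule and analysis are untouched, and emergency access through the envelopes stays as it is. If absence of the person preparing the medication is a worry, the external provider could act as the second holder. The article does not say whether the provider keeps a copy, so that would have to be confirmed.

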### Outcome assessments

For an overview of frequency and timing of outcome assessment, see Fig. 1.

The *primary outcome* comprises change from baseline to post-treatment on a cognitive composite score assessing attention, verbal learning and memory, and executive functions. We have found an improvement on this “speed of complex cognitive processing” composite measure in our previous EPO cognition trial across patients with BD and TRD after 8 weeks of weekly EPO treatment [31]. In the present study, we therefore include the same global cognition score as the primary outcome measure. This consists of the following six neuropsychological tests, spanning verbal memory, attention, and executive functions: Rey Auditory Verbal Learning Test (RAVLT) [32, 33], the Repeatable Battery for the Assessment of Neuropsychological Status (RBANS) Coding [34], Verbal Fluency with the letter “D” [35], Wechsler Adult Intelligence Scale (WAIS)-III Letter-Number Sequencing [36], Trail Making Test Part B (TMT-B) [37], and Rapid Visual (Information) Processing (RVP) from the Cambridge Neuropsychological Test Automated Battery (CANTAB Cognition Ltd.). The secondary outcomes are retrograde autobiographical memory measured with the Columbia University Autobiographical Memory Interview-Short Form (AMI-SF) [38, 39] and verbal learning and memory assessed with the RAVLT [32, 33]. The tertiary outcomes comprise (1) individual neuropsychological tests of the cognitive composite score, (2) depression severity assessed with the HDRS-17 [27] and the Beck Depression Inventory, 21 items (BDI-21 [40]), respectively, (3) subjectively rated cognitive complaints assessed with the Cognitive Complaints in Bipolar Disorder Rating Assessment (COBRA) [41], (4) cognition-related activity in key neuronal circuits and hippocampal structure, and (5) blood- and urine-based markers of inflammation, oxidative stress, and neuroplasticity. History of early life stress will be assessed with the Childhood Trauma Questionnaire (CTQ [42]) at the eligibility assessment.

To reduce risks of learning effects at follow-up neuropsychological assessments, we administer alternate versions of the RAVLT (original list AB, GeAB, and Cr-AB) and RBANS Coding (version A and B) [34] in a counterbalanced order within each stratum.

### Peripheral and neural biomarkers and genotyping

To investigate whether there is a significant difference between EPO- and saline-treated patients in structural and functional measures of cognition-relevant neural regions, including the hippocampus and the frontal lobes, patients undergo a structural and fMRI scan after 3 weeks of weekly EPO or placebo infusions (i.e., at week 4). During fMRI (approximately 45 min duration) patients are given three neurocognitive tests: (1) the Autobiographical Memory Test [43] adapted for fMRI assessment [13, 44], (2) a hippocampus-dependent picture memory retrieval test that is sensitive to the effects of EPO on hippocampal response [17], and (3) a Spatial N-back working memory test from our previous study [19]. Furthermore, we will examine whether the potential protective effects of EPO on cognition are accompanied by changes in markers of oxidative stress, inflammation, or neuroplasticity in blood and urine. Specifically, blood samples will be analyzed to investigate whether changes in the peripheral biomarker, high-sensitivity C-reactive protein (hsCRP), are important for cognitive benefits of EPO treatment.

### Biochemistry

Since EPO has anti-inflammatory actions [14, 22, 23] and compiling evidence indicates that major depressive disorder (MDD) is associated with increased low-grade neuroinflammation [45–47], we will explore the effects of add-on treatment with EPO on systemic markers of inflammation. Blood and urine samples will be transferred to the Neuropsychiatric Laboratory, Department O, Rigshospitalet, and stored at − 80 °C until use. Measurements will be performed at the Neuropsychiatric Laboratory and at the Department of Clinical Pharmacology, Rigshospitalet.

### Statistical analyses

The statistical significance threshold is considered to be *p* < 0.05 (two-tailed). Behavioral, mood, and biomarker data will be analyzed using a mixed models design and an intention-to-treat (ITT) approach. Structural and functional imaging data will be collected using a 3 T MR scanner operating at Copenhagen University Hospital, Rigshospitalet. Resting state and task-related fMRI data will be preprocessed and analyzed using the FMRIB Expert Analysis Tool (FEAT) and the ‘randomize’ algorithm integrated in the FMRIB Software Library (FSL), www.fmrib.ox.ac.uk/fsl. We will adjust for potential differences in demographical and clinical parameters at baseline. All statistical analyses will be run using the *Statistical Package for Social Sciences* (SPSS, version 23, IBM Corporation, Armonk, NY).

#### Sample size and power calculation

The sample size and statistical power have been calculated by Pharma Consulting Group AB using PROC POWER and the SAS code in SAS version 3. We estimate that a clinically relevant differential change in the cognitive composite score between the EPO and placebo groups is 0.4 standard deviations (SD; corresponding to a moderate effect size), with an SD of the mean change of 0.5. This is consistent with the recommendations of the International Society for Bipolar Disorders (ISBD) cognition task force [48]. Specifically, the task force noted that a differential change between groups of 0.2–0.4 SD on a global composite score represents a potentially clinically relevant change, as this may translate into moderate to large functional improvement in patients with mood disorders [48]. In our previous 8-week EPO trial, the difference between EPO and the saline groups regarding change in the cognitive composite score from baseline to post-treatment was 0.5 SD [31]. Based on the ISBD task force recommendations and our previous findings regarding the effects of longer term EPO treatment, we estimate that a sample size of *N* = 52 (*n* = 26 per group) will reach a ≥ 0.8 power to detect a similar clinically relevant differential change of 0.4 SD in the primary outcome measure (the cognitive composite score) with an SD of this change of 0.5 between the two groups at an alpha level of 5% (two-sided test) [31].

The study is also powered to investigate differences in fMRI blood-oxygen-level dependent (BOLD) response in key neural networks based on our previous fMRI studies, in which sample sizes of 30 age- and gender-matched participants (*n* = 15 per group) had a power of > 0.8 to show drug-related effects on task-related neural response (e.g., memory and executive function) at an alpha level of *p* < 0.05 [19, 31]. In the current trial, the inclusion of 52 participants (*n* = 26 per treatment group) therefore ensures sufficient statistical power to detect EPO-related effects on neural activity.

